#### Priority interventions

All patients allocated to the Intervention group will be offered the ‘priority’ interventions. These interventions are recommended by the NICE Clinical Guidelines for the management of all people with knee OA [12]. While patients are strongly encouraged to undertake all the priority interventions recommended by the CST, it is ultimately their decision on the interventions to undertake. The priority interventions include:*Education:* provision of OA educational resources compiled by the PARTNER team and our partner organisations, as well as links to Arthritis Australia’s OA consumer website ‘*myjointpain.org.au*’ and the ‘pain*HEALTH*’ website, [44, 45] a brochure introducing the CST and a range of other information sources and other self-monitoring tools.

b.*Muscle strengthening program:* A physiotherapist-developed home exercise program for leg strengthening which includes the common exercises used to strengthen the thigh and buttock muscles, and provides tips for progressing the exercises and how to stay motivated with an exercise program. Patients will be provided with exercise resistance bands to assist them to progress. This program will be provided by the CST.

c.*Physical activity plan:* the CST will help the patient with strategies to increase their incidental and general physical activity levels.

d.*Weight loss advice and support*: If the patient has a BMI ≥27 kg/m^2^, the patient will be offered the option of participating in the remotely-delivered “Healthy Weight for Life®” weight loss program which has been shown to be effective in people with OA [32]. The program is an 18-week, three-phase approach provided by PRIMA Healthcare, and involves a very low-calorie diet (KicStart™), a portion-controlled eating system, an exercise program, and educational resources on a healthy diet and lifestyle. After the 18-weeks patients will be referred back to the PARTNER CST, and if required can continue to be provided with weight loss advice until the end of the intervention period. Patients who do not wish to undertake the HWFL program, or are not eligible for the program, will continue to be managed by the CST throughout the whole intervention period, as described above. They will be offered all other relevant components of the intervention.
e.*Medication review:* Patients will be offered a review of their current OA medications. This should be undertaken by the GP at the initial consultation, however their medications will continue to be discussed by the CST, using an algorithm previously developed for Arthritis Australia’s *myjointpain.org.au* website*.* Patients will be encouraged to speak to their GP or local pharmacist if they require a medication review.

#### Secondary interventions, online management tools and community run services

Patients may also be directed to one or more online tools, or community run services for the management of different aspects of their OA. The online tools have been developed by experts in their field. Referral to these online services will be offered if the patient meets the pre-determined criteria for stepping up care and/or has identified as their priority for action. These components are *optional* for the patient and include:

Advice on mobility aides or secondary therapies such as walking sticks, orthoses, or heat pads.*Pain coping skills training*: an online 8-week Cognitive Behavioural Therapy (CBT) program for pain coping skills training which has been shown to be effective in knee OA [46]. The pain coping skills training program is an online program comprised of eight modules that provide interactive training in cognitive or behavioural pain coping skills. It is being provided free of charge for patients in the study.*Depression - This Way Up*: an online CBT program for education and treatment of anxiety and depression [47]. It will be offered to intervention patients in the study free of charge [48].*Insomnia and sleep – SHUTi*: the online CBT program “SHUTi” was designed to help people with insomnia identify and change thoughts or behaviours that influence sleep patterns [49]. The course is offered in Australia through the Black Dog Institute [50]. The completion of this course is optional and would be at an additional cost.*Community-based services and facilities*: Depending on the patient’s preference for service delivery (e.g. group vs individual), they may be directed to services or facilities run by community groups or other commercial entities, such as exercise classes, public gyms or other sporting organisations. These options would be at an additional cost.*Work productivity*: If patients self-report a decrease in their work productivity due to their knee OA they will be given the option of being referred to a vocational counsellor in their area. This option would be at an additional cost.

### Usual care

Patients in the control group will be asked to visit their GP for an initial consultation. GPs will not refer their patients to the CST, but will manage the patient’s OA in their usual manner (usual care). Management of the patient’s OA is purely at the discretion of the GP. GPs will only receive a brief introduction to the study. GPs may refer to any third-party provider, which may incur additional out-of-pocket expenses. Patients may attend these services at their own discretion and cost. Once the GP in this group has completed their involvement in the study (i.e. all of their patients have had their final follow-up assessment), they will be offered the opportunity to undertake the training and professional development opportunities offered to the GPs in the intervention group. The exception would be the provision of the cdmNet software and training.

### Outcome measures

Table 1 summarises the primary and secondary outcome measures. The outcomes include patient-level validated measures recommended for OA by the Osteoarthritis Research Society International (OARSI) and International Consortium for Health Outcomes (ICHOM) [51, 52], or have been used in other similar trials. Patients will be asked to nominate their most symptomatic knee (provided it has not undergone arthroplasty), which will be considered their “study knee” for the duration of the trial. Primary and secondary outcome data will be collected at baseline, 6 and 12 months after enrolment and are self-reported unless otherwise specified in Table 1. 24-month follow-ups will also be conducted. The two primary outcomes are:Change in average knee pain at 12 months: overall average pain over the past week self-reported via an 11-point NRS with terminal descriptors of ‘no pain’ (score 0) and ‘worst pain possible’ (score 10).

**Table 1 Tab1:** Summary of primary and secondary data collected from study patient participants to determine intervention effectiveness

Outcome	Measurement tool
Primary Outcome Measures	
Knee pain	11-point numerical scale
Knee function	Knee injury and Osteoarthritis Outcome Score (KOOS) - function in daily living subscale
Secondary Outcome Measures	
Knee pain	KOOS pain subscale
Knee function	KOOS - function in daily living subscale
Knee OA symptoms	KOOS - other symptoms subscale
Knee function with sport and recreation	KOOS - function with sport and recreation subscale
Knee quality of life	KOOS - knee-related Quality of Life subscale
Weight and BMI (calculated)	Self-report
Health-related quality of life	Assessment of Quality of Life (AQoL-8D)
Depression	Patient Health Questionnaire (PHQ 9)
Sleep impairment	PROMIS adult Sleep-Related Impairment Short Form 8a
Fatigue	PROMIS Fatigue Short Form 8a
Global rating of change	7-point numerical rating scale
Satisfaction, overall with treatment	7-point numerical rating scale
Satisfaction with change in symptoms	7-point numerical rating scale
Work productivity	Work Productivity and Activity Impairment Questionnaire: Osteoarthritis of the Knee V2.0 (WPAI:OA)
Health Care Expenditure	Medicare Benefits Schedule (MBS) and Pharmaceutical Benefits Scheme (PBS) data.
Economic evaluation of the cost-effectiveness of the intervention	Based on the Assessment of Quality of Life (AQoL-8D)

2.Change in physical function of the knee at 12 months: knee function will be measured using the function in daily living subscale of the Knee injury and Osteoarthritis Outcome Score (KOOS) [53]. The KOOS questionnaire measures symptoms and functional limitations associated with knee OA using patient-reported outcome measures. The questionnaire consists of five subscales; pain, other symptoms, function in daily living (ADL), function in sport and recreation (Sport/Rec) and knee-related Quality of Life (QOL), measured using Likert responses scored from 0 to 4. The questions pertain to the previous seven days. The KOOS is a widely used disease-specific instrument whose validity, reliability and responsiveness have been demonstrated in a range of OA studies [54].

Our secondary outcome measures are:Change in knee pain at 6 months: overall average pain over the past week will be self-reported via a NRS and the pain sub-scale of the KOOS (as described above).Change in physical function of the knee at 6 months: will be measured using the *Function (Activities of Daily Living)* subscale of the KOOS.

3.Change in other OA symptoms of the knee at 6 and 12 months will be measured using the *Symptoms* subscale of the KOOS.

4.Change in QoL at 6 and 12 months will be measured using the *Quality of Life* subscale of the KOOS.

5.Change in function of the study knee during sport and recreational activities at 6 and 12 months will be measured using the *Function (sports and recreational activities)* subscale of the KOOS.6.Change in weight and BMI at 6 and 12 months. BMI will be calculated using baseline height data. Patients will be asked to use the same set of scales to measure their weight for all time points. It is recommended that these outcomes are assessed for all OA clinical trials that target symptom-modifying interventions [51].7.Change in health-related QoL at 6 and 12 months will be assessed via the *Assessment of Quality of Life* (AQoL-8D) [55]. The AQoL-8D is a health-related multi-attribute utility quality of life instrument, initially designed for use in economic evaluation studies. This instrument has 35 items in 8 separately scored dimensions; independent living, relationships, mental health, coping, pain, senses, self-worth and happiness. The questions pertain to the previous 7 days.8.Change in depression (mood) at 6 and 12 months will be measured using the *Patient Health Questionnaire* (PHQ9) [56]. The PHQ9 is a multi-purpose instrument for screening, diagnosing, monitoring and measuring the severity of depression. It is used widely for identifying depression in chronic conditions including OA. There are nine questions scored on a 4-point scale (0 = not at all, 3 = nearly every day). The questions pertain to the previous 14 days. Score responses are *normal*, *mild*, *moderate*, *moderately severe, severe* and *very severe*. Any patient with a classification of *severe* or above, or presents with thoughts of self-harm, will be referred back to their GP for their follow-up.9.Sleep impairment at 6 and 12 months will be measured using the *Patient-Reported Outcomes Measurement Information System* (PROMIS™) adult Sleep-Related Impairment Short Form 8a (patient self-report) [57]. The tool consists of eight questions that ask patients to rate their perceptions of alertness, sleepiness, and tiredness during usual waking hours, and the perceived functional impairments during wakefulness associated with sleep problems or impaired alertness. The questions pertain to the previous seven days. Five response options are used ranging in value from 1 (not to all) to 5 (very much). The total raw score is calculated by the sum of values of the response to each question (min 8, max 40).10.Change in fatigue at 6 and 12 months will be measured using the *PROMIS*™ Short Form 8a (patient self-report) [57]. The tool consists of eight questions that ask patients to rate their perceptions of fatigue symptoms ranging from mild subjective feelings of tiredness to an overwhelming, debilitating, and sustained sense of exhaustion that likely decreases one’s ability to execute daily activities and function normally in family or social roles. Fatigue is divided into the experience of fatigue (frequency, duration, and intensity) and the impact of fatigue on physical, mental, and social activities over a 7-day period. Five response options are used ranging in value from 1 (not to all) to 5 (very much). The total raw score is calculated by the sum of values of the response to each question (min 8, max 40).11.Change in patient’s global rating of change in knee OA at 6 and 12 months. Patients will be asked to rate their overall perceived change in OA on a 7-point scale ranging from “much worse” to “much better”.12.Satisfaction with treatment will be measured at 6 and 12 months on a 7-point scale ranging from “extremely unsatisfied” to “extremely satisfied”.(47)

13.Satisfaction with change in knee OA symptoms (outcome) will be measured at 6 and 12 months on a 7-point scale ranging from “extremely unsatisfied” to “extremely satisfied” [58].
14.Change in lost productivity at 6 and 12 months will be measured using the *Work Productivity and Activity Impairment Questionnaire*: Osteoarthritis of the Knee V2.0 (WPAI:OA) [59]. This instrument measures the time away from work because of knee OA and the effect of knee OA on productivity while at work. The questions pertain to the previous seven days.

15.Healthcare expenditure will be extracted from the MBS and PBS data. Medicare data includes information on medical visits and procedures, and the associated costs and PBS data includes information on prescription medicines filled at pharmacies. We will seek patients’ consent to access their MBS and PBS data from the Australian Government Department of Human Services (DHS, approval no. MI7185). A structured health diary will be used to collect other health services on the use of services not included in MBS and PBS data such as hospitalisation, non MBS-funded allied health service use and over the counter medications.16.Economic evaluation of the cost effectiveness of the intervention.

#### Additional measures

A range of additional measures (using both quantitative and qualitative methods) will be collected for the purposes of answering questions about the potential mediation of treatment effects, referrals to other health professionals and utilisation of other services, barriers and facilitators to implementing the intervention, fidelity of the training provided, long-term implementation needs and economic analyses (Table 2). These analyses will not be used to measure treatment effectiveness. Specific instruments used include:

**Table 2 Tab2:** Summary of other data collected from study patient participants. Baseline survey collected at 0 months

Outcome	Measurement tool	Collected at
Mediator measures		
Physical activity levels	Physical Activity Scale for the Elderly (PASE)	0, 6 and 12 months
Fear of movement	Brief Fear of Movement Scale (BFMS)	0, 6 and 12 months
Pain catastrophising	Pain Catastrophising Scale (PCS)	0, 6 and 12 months
Pain coping skills	Coping Strategies Questionnaire (CSQ)	0, 6 and 12 months
Ability to manage their condition	Effective Consumer Scale (EC17)	0, 6 and 12 months
Perception of their OA	Brief Illness Perception Questionnaire (B-IPQ)	0, 6 and 12 months
Arthritis self-efficacy	Arthritis Self-Efficacy Scale (ASES)	0, 6 and 12 months
Other patient collected data		
Post GP visit questionnaire	Custom questionnaire	Immediately after GP visit, ~ 2–6 weeks
Quality of OA care delivered during study	Osteoarthritis Quality Care Indicator (OA-QI)	6 and 12 months
Patient activation or self-management attitudes	Patient Activation Measure (PAM)	0 months
Treatment expectation	Custom questionnaire	0 and 6 months
Willingness for surgery	Custom questionnaire	0, 6 and 12 months
Participation in study components	Custom questionnaire	0, 6 and 12 months
Intervention adherence questions	Custom questionnaire	6 and 12 months
Adverse events	Custom questionnaire	0, 6 and 12 months

Change in physical activity levels measured with the *Physical Activity Scale for the Elderly* (PASE), at 6 and 12 months. The PASE is a 10-item questionnaire used to measure both the frequency and type of recreational and occupational physical activity undertaken by participants over the previous seven days. Higher scores indicate greater levels of physical activity. The PASE was developed and validated in samples of older adults ≥ 55 years of age and has been used in many OA clinical trials [60].

b)Change in patient’s fear of movement and activity measured with the *Brief Fear of Movement Scale for Osteoarthritis* [61] at 6 and 12 months. The questionnaire consists of six statements and patients are asked to indicate how much they agree or disagree with each statement. The four response options range in value from 1 (strongly disagree) to 4 (strongly agree).

c)Change in patient’s pain catastrophising measured with the *Pain Catastrophizing Scale* (PCS) [62] at 6 and 12 months. The instrument is widely used in both clinical practice and research. The PCS is a 13-item instrument designed to quantify an individual’s pain experience and measure catastrophic thinking related to pain. Patients will be asked to indicate the degree to which they have the above thoughts and feelings when they are experiencing pain on a five point response scale ranging from 0 (not at all) to 4 (all the time). A total score is obtained (0–52), and can also be divided into three subscales that assess rumination, magnification and helplessness.

d)Change in patient’s pain coping skills at 6 and 12 months. This is measured using the *Coping Strategies Questionnaire* (CSQ) [63] at 6 and 12 months. The CSQ can be used to measure how often a patient uses six cognitive and behavioural pain coping strategies to manage pain (diverting attention, re-interpreting pain sensations, coping self-statements, ignoring pain sensations, praying and hoping, and increasing activity level). We will use the coping attempts subscale comprising 17 questions. Items are measured on a 7-point Likert scale (where 0 = never uses coping skills and 7 = always uses coping skills). Higher scores indicate greater coping skills. Based on prior factor analyses of this instrument [63] participant’s responses will be converted to scores on the Coping Attempts factor of the CSQ. The CSQ has demonstrated sensitivity to change from treatment in samples of people with chronic pain as well as good internal consistency and construct validity.

e)Change in patient’s ability to manage their condition at 6 and 12 months: The *Effective Consumer Scale* (EC17) will be used to determine how effective people are at dealing with their chronic condition and how well they make decisions about their health care [64]. This 17-item instrument has been validated in patients with arthritis diseases and comprises five domains looking at i) use of health information, ii) clarifying personal priorities, iii) communicating with others iv) negotiating roles and taking control, and v) deciding to take action. It is measured on a five-point scale with responses ranging from 0 (never) to 4 (always).

f)Change in patient’s perceptions of their OA at 6 and 12 months. The *Brief Illness Perception Questionnaire (B-IPQ)* [65] will be used to assess changes in the patient’s perception of their condition. The B-IPQ is an eight-item instrument that measures the cognitive perceptions with respect to a condition on an ordinal scale (0–10). The areas examined are: i) consequences, ii) timeline, iii) personal control, iv) treatment control, v) identity for describing the condition and symptoms, vi) coherence, and vii) concern and emotions. The maximal score is 80, with higher scores reflecting more negative perceptions.g)Change in patient self-efficacy will be measured using the short form eight item *Arthritis Self-Efficacy Scale* (ASES) at 6 and 12 months [66]. It will be administered at baseline, 6 and 12 months. The 8-item short form is a validated version of the original version, and was designed to take less time for trial participants to complete. The participant is asked how certain they are that they can do the following tasks at the present time. The instrument includes two items on pain, four items on other symptoms, and two items that relate to preventing pain and fatigue from interfering with daily activities. Each question is ranked on a scale of 1–10 ranging from 1 “very uncertain” to 10 “very certain”. The total score is the mean of the eight items.

#### Economic evaluation

An economic evaluation will be conducted from the health care system perspective. We will assess cost-effectiveness of the intervention analysing a range of outcomes including incremental cost per extra person with a clinically significant improvement in pain (measured as 1.8 point reduction on the 0–10 pain score) and per quality-adjusted life years (QALYs) gained for the intervention group compared to the control group at 12 months. QALYs will be calculated based on utility scores using the AQoL-8D at baseline, and 12 months. We will compare the differences in health care usage and utility gains on the AQoL-8D over 12 months between intervention and control groups (adjusting for any difference in the baseline values between the groups). We will also compare changes in productivity lost from baseline to 12 months between the intervention and control groups.

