Phase 1 – first 18 weeks. The patient will be contacted once per fortnight on average, or as agreed with the patient. The CST will provide ongoing self-management advice and support, to address the goals and activities of their tailored care plan.

2.Phase 2–6 month maintenance period (or until the end of the 12-month intervention period). Patients will be encouraged and supported to develop strategies to self-manage their OA. They will be contacted monthly, or as agreed, to monitor their progress and address any new or ongoing issues as required. Patients can still be re-referred to their GP or other allied health professionals if an escalation of care is required. However, patients cannot elect to participate in the HWFL weight-loss program during this phase.

The CST will provide updates to the GPs on the progress of their referred patients via cdmNET at three time points (after initial consultation, after 18 weeks and at the end of the patient’s involvement with the CST), or on request by the GP. The reports will detail any strategies and actions agreed with the patient, and their progress to date. The CST will refer the patient back to their GP if they require a medication review, or if they have any other medical condition that affects participation in the trial or an escalation of care. If the situation is urgent the CST member will ring the GP to discuss. If the situation is routine the CST will correspond with the GP via cdmNET.

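### The QALY rule uses AQoL-8D at baseline and 12 months only, although the 6-month value is also collected, so the QALY gain and cost per QALY can be misstated in either direction

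*Protocol article*

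**What the plan says.** The Economic evaluation section (under Additional measures) names the time points for the QALY: "QALYs will be calculated based on utility scores using the AQoL-8D at baseline, and 12 months". The horizon and contrast are "quality-adjusted life years (QALYs) gained for the intervention group compared to the control group at 12 months", and the comparison of utility gains is made "adjusting for any difference in the baseline values between the groups". No interpolation rule is given.

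The Outcome measures section sets a wider collection schedule: "Primary and secondary outcome data will be collected at baseline, 6 and 12 months after enrolment". Secondary outcome 7 repeats it for this instrument: "Change in health-related QoL at 6 and 12 months will be assessed via" the AQoL-8D. The same item explains what the instrument is for: "The AQoL-8D is a health-related multi-attribute utility quality of life instrument, initially designed for use in economic evaluation studies". Table 1 lists both the AQoL-8D and the economic evaluation based on it as secondary outcomes.

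On the intervention, the section on the PARTNER care support team describes a first phase of 18 weeks in which "The patient will be contacted once per fortnight on average, or as agreed with the patient", followed by roughly monthly contact until the end of the 12 months.

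**The concern.** A utility measurement that is scheduled for every patient, from an instrument built for economic evaluation, is left out of the one calculation that most needs it. A QALY difference over 12 months is an area between two utility curves. With only the two end points, whatever happened in between has to be assumed, and a two-point result cannot respond to the 6-month value under any interpolation rule.

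The contact schedule makes this more than a formality. Support is denser in the first 18 weeks, and the optional weight-loss programme also runs for 18 weeks. A benefit that arrives early and then holds or fades is therefore a real possibility, and a two-point rule would under-count it. A benefit that builds late would be over-counted.

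At stake is the cost per QALY. The article names cost-effectiveness beside effectiveness in its aim, and the Discussion ties both to policy recommendations.

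**Working it through.** The document states no utility, QALY or cost-per-QALY figure, so there is nothing to reproduce. The check compares the stated rule with the one that the collected data allow.

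**Inputs from the document**
- QALY time points: baseline and 12 months (Economic evaluation).
- Collection time points: baseline, 6 and 12 months (Outcome measures, general schedule and secondary outcome 7).
- Horizon: 12 months, intervention against control (Economic evaluation).
- Baseline difference: adjusted for, so taken as 0 (Economic evaluation).

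**Assumptions**
- Linear change between measured points (trapezium rule). The document does not state this.
- d6 and d12, the between-arm utility differences at 6 and 12 months, are not given and are varied below. d12 is positive except where stated.
- The incremental cost is the same under both calculations.

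**Formulas, time in years**
- Two points: 1 × (0 + d12)/2 = 0.5 × d12.
- Three points: 0.5 × (0 + d6)/2 + 0.5 × (d6 + d12)/2 = 0.5 × d6 + 0.25 × d12.
- Error, two-point minus three-point: 0.25 × d12 − 0.5 × d6. This is zero only if d6 = d12/2.
- Cost per QALY, two-point relative to three-point: (0.5 × d6 + 0.25 × d12)/(0.5 × d12).

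**Results by assumed d6/d12**

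| d6/d12 | Two-point gain ÷ d12 | Three-point gain ÷ d12 | Two-point gain relative to three-point | Cost per QALY, two-point relative to three-point |
|---|---|---|---|---|
| 0 | 0.5 | 0.25 | 2.00 | 0.50 |
| 0.25 | 0.5 | 0.375 | 1.33 | 0.75 |
| 0.5 | 0.5 | 0.5 | 1.00 | 1.00 |
| 1 | 0.5 | 0.75 | 0.67 | 1.50 |
| 1.5 | 0.5 | 1.0 | 0.50 | 2.00 |
| 2 | 0.5 | 1.25 | 0.40 | 2.50 |

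**Illustrations with an assumed incremental cost of 1,000 per person**
- d6 = d12 = 0.04: 0.020 against 0.030 QALY, so 50,000 against 33,333 per QALY.
- d6 = 0.01, d12 = 0.04: 0.020 against 0.015 QALY, so 50,000 against 66,667 per QALY. The error has reversed.
- d6 = 0.04, d12 = 0: 0 against 0.020 QALY. The two-point rule records no gain, and its cost per QALY is undefined.

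**Timing of the intensive phase.** The 12-month period starts when the baseline survey is complete (Recruitment), and first contact with the support team comes about one month later. If the 18 weeks run from that contact, they end at about 4 + 18 = 22 weeks, against 26 weeks for the 6-month survey. That survey therefore falls shortly after the intensive phase, where it is informative about the path of utility. The timing does not say what the path will be.

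**The case against.** The strongest reply is that this is a drafting slip. The comma before the last time point in the QALY sentence is consistent with a 6 having dropped out, and the next sentence speaks of utility gains over the whole 12 months. That may be so, but the text as it stands names two time points, conflicts with the collection schedule, and needs the same correction either way. Nor is it a detail left to a fuller plan, because the article does not stay silent: it fixes the time points.

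Other parts of the case against limit how far the point can be taken.

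- A reader might infer from the denser early contact that straight-line change is the least plausible path. The document does not show this. First contact lags enrolment by about a month, support continues monthly to month 12, the main targets (strengthening, activity, weight) can change gradually, and the weight-loss programme is optional and limited to patients with a BMI of 27 or more. A 6-month difference close to half the 12-month difference, where both rules agree, cannot be ruled out.
- A reader might infer that the 6-month data are thrown away. They are not: they are assessed under secondary outcome 7 and are missing only from the QALY sentence.
- Linear interpolation is the usual convention, not something that the article states. The sizes above depend on it.

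**Conclusion.** The point stands as a mismatch between the QALY rule and the collection schedule. Followed as written, the rule gives a less accurate QALY difference and cost per QALY than the collected data allow, and no reason is offered.

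The size depends on utility differences that the document does not give. Under linear interpolation, with the baseline difference adjusted to zero, the two-point rule understates the gain by one third if d6 = d12 and by 60% if d6 = 2 × d12. It overstates the gain 2-fold if d6 = 0, which is the upper limit for overstatement as long as d6 is not negative and d12 is positive. The stronger reading, that the plan will under-count the benefit and make the intervention look too expensive, goes beyond the document: the contact schedule makes that a real possibility, but the error reverses whenever d6 is less than half of d12.

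Confidence is high for the mismatch and the algebra, and low for the direction and size in this trial. The reach is limited to the QALY-based results. Neither primary outcome is affected, nor is the cost per extra person with a clinically significant improvement in pain.

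**What to change.** In the Economic evaluation section, replace the QALY sentence with one stating that QALYs are the area under the AQoL-8D utility curve through baseline, 6 and 12 months, by the trapezium rule. Keep the baseline adjustment already stated there, and apply the multiple imputation of missing participant-level data already planned under Statistical analysis to missing 6-month utilities as well. The two-point version may be kept as a labelled sensitivity analysis.

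The cost is one sentence. No new data, visits or questionnaires are needed. The change is best made before results by arm are seen, so that nobody later has to choose between two QALY figures.
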